### 5.1.8 Other analysis

We will consider conducting falsification analyses (negative controls) for alternative outcomes (e.g. non-COVID hospitalisations) if data allow.

## 5.2 Missing data

Missing data will be reported as percentages of total or raw numbers where possible. For covariates that may have a higher proportion of missing data, we will either use records with no item missingness or use a missing category.

## 5.3 Statistical software

All analyses will be carried out using R/RStudio using the following packages: tidyverse^4^, Epi^5^, survival^6^, mgcv^7^, popEpi^8^

# Reporting results

## 6.1 Reporting guidelines and conventions

Results will be reported according to the Strengthening the Reporting of Observational Studies in Epidemiology (STROBE) and REporting of studies Conducted using Observational Routinely-collected Data (RECORD) guidelines. Measures of the association will be interpreted based on 95% confidence intervals.

## 6.2 Dissemination

This statistical analysis plan will be made publicly available on a website prior to conducting the main statistical analyses. The results will be written in a manuscript and submitted to a peer-reviewed journal. We will also seek to provide feedback to relevant COVID-19 advisory bodies (e.g. UK Joint Committee on Vaccination & Immunisation, Brazilian Ministry of Health, WHO) as appropriate. All code will be made publicly available via a GitHub repository.

# Appendix

## **Table S1. ICD-10 codes**

| **Code** | **Description** | **Category** |
| --- | --- | --- |
| U07.1 | COVID-19, virus identified | U07.1 |
| U07.2 | COVID-19, virus not identified | U07.2 |
| Source:<https://www.who.int/classifications/icd/COVID-19-coding-icd10.pdf> | | |

1. Rapid antigen test will be evaluated only in Brazil [↑](#footnote-ref-0)
2. Brazilian data will use only time between test and date of death, while Scotland will use ICD Codes and time between test and date of death and ICD-10 codes in the death record. [↑](#footnote-ref-1)
3. The first band is 7 years: 18-24, the last band is 90+ [↑](#footnote-ref-2)

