## 2.2 Objectives

By vaccine type, we seek to:

1. Estimate Odds Ratio (OR) against the composite outcome of COVID-19 hospitalisation/death of individuals with booster dose versus individuals without booster dose.
2. Estimate Odds Ratio (OR) against confirmed SARS-CoV-2 infection of individuals with booster dose versus individuals without booster dose.
3. Estimate Rate Ratio (RR) against the composite outcome of COVID-19 hospitalisation/death as a function of time post maximum effect of the booster dose of a COVID-19 vaccine.
4. Estimate RR against the separate outcomes of i) COVID-19 hospitalisation; ii) COVID-19 death as a function of time post maximum effect of the booster dose of a COVID-19 vaccine.
5. Assess if waning of protection from booster dose differs by age group, sex and being in a high-risk COVID-19 group

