# Study Design

## 3.1 Study design

Objectives a) and b) will be evaluated through a test-negative design case-control study

Objective c) and d) open prospective cohort study comparing outcomes amongst vaccinated people for differing lengths of time.

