## 3.5 Inclusion/exclusion criteria

Inclusion criteria for the primary cohort:

- Receive at least two doses of BNT162b2 or ChAdOx1 before or during the study period.

Exclusion criteria for the primary cohort:

- Inconsistent vaccination records (i.e. received a second dose with no record of a first dose, received doses from different vaccine types or interval between doses of less than 14 days)
- Missing essential covariates (sex, age, geography)
- Children (under the age of 18 years)
- Hospitalization previous to the study start date
- A positive test within 28 days of the study start date

Inclusion criteria for the TND:

- Receive at least two doses of BNT162b2 or ChAdOx1 at the sample collection date.

Exclusion criteria for the TND:

- Tests within 90 days of a previous positive test
- Negative tests followed by a positive test within 7 days
- Negative tests within 14 days of a previous negative test
- Missing essential covariates (sex, age, geography)
- Children (under the age of 18 years)

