### 5.1.2 Outcomes of interest

The primary outcome will be a composite outcome of time to COVID-19 hospitalisation or death. COVID-19 hospitalisation will be defined as a RT-PCR confirmed positive test for SARS-CoV-2 in the 14 days prior to admission, or with ICD-10 code for COVID-19 (in any diagnostic position).

COVID-19 deaths will be defined as COVID-19 as the underlying ICD-10 cause of death recorded on the death certificate or death recorded in SIVEP-Gripe^^[[2]](#footnote-1)^^ within 28 days of a confirmed positive test.

Secondary outcomes will be the single outcomes of: i) COVID-19 hospitalisation, ii) COVID-19 deaths, iv) RT-PCR confirmed positive test, provided numbers of events allow. We anticipate the RT-PCR confirmed SARS-CoV-2 infection results to be more susceptible to bias arising from differential ascertainment, and therefore anticipate treating these results as more tentative.

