### 5.1.5 Analytical techniques

We will commence analysis by conducting descriptive analyses to visually inspect trends in vaccination delivery, age-specific COVID-19 hospitalisations and COVID-19 deaths, including by age group and sex. This will include checking the number of people who have received two doses and the length of follow-up available following the second dose by vaccine type. Including plotting Lexis diagram to afford for the correlated structure of the data (Calendar Time/Length of Follow-up)

For the analysis consisting of individuals with at least two doses, we will stratify the cohort based on the month of the second dose of each individual. The vaccination status will be classified as:

- Second dose:
  - <2 weeks
  - 2-9 weeks
  - 10-19 weeks
  - ≥20 weeks without a booster dose [Reference Period]
- Booster dose:
  - <2 week
  - 2-4 weeks
  - 5-8 weeks
  - 9-12 weeks
  - ≥13 weeks

This variable will be used to fit a Poisson regression to obtain rate ratios (RRs) and their 95% confidence intervals (CIs). If we observe overdispersion, we will consider using Negative Binomial regression models or Poisson with robust standard errors. Models will be adjusted for the relevant confounders above, including a set of dummy variables for calendar week.

The models will be fit to a dataset with all events and a random sample, without replacement, of 100 individuals per event (for hospitalisation and death, 10 for positive tests). The sample weights will be calculated to represent the sampling fraction, thus ensuring the correct calculation of the person-years at risk for the whole population.

The primary analysis for the test negative will be on individuals who are symptomatic at the time of test and the date of symptom onset is 0-10 days before the test. We will then establish the number of weeks post-vaccination for the cases and controls calculated as time between sample collection date and vaccine dose. The odds' ratio will be calculated using a logistic regression. Adjusted for: race/ethnicity, comorbidities, dummy variables for calendar week, age (five-year bands), sex. Controls will be defined based on a negative test.

We will also construct a propensity score to be tested among those in the primary cohort and use this as an inverse propensity weight.

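### The primary-outcome hospitalisation can rest on ICD-10 code U07.2 (COVID-19 without an identified virus) alone, and no planned analysis shows the result without it

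*SAP*

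**What the plan says.** SAP section 5.1.2 sets the primary outcome: "The primary outcome will be a composite outcome of time to COVID-19 hospitalisation or death". An admission qualifies by either of two routes. One is a positive RT-PCR in the 14 days before admission. The other is a code: "or with ICD-10 code for COVID-19 (in any diagnostic position"). The code route asks for no test result.

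Table S1 in the Appendix is the only ICD-10 list in the document. It has two entries, U07.1 (virus identified) and "U07.2 | COVID-19, virus not identified | U07.2". Nothing ranks one below the other. Section 5.1.2 also accepts an ICD-10 underlying cause for COVID-19 deaths. Footnote 2 says that, for deaths, Scotland uses ICD codes and Brazil uses only the time from test to death.

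For the case-control part, section 3.1 says "Objectives a) and b) will be evaluated through a test-negative design case-control study". The first objective in 2.2 is "Estimate Odds Ratio (OR) against the composite outcome of COVID-19 hospitalisation/death". In 5.1.5, "Controls will be defined based on a negative test". Section 3.5 removes "Negative tests followed by a positive test within 7 days" and also tests that fall too soon after an earlier one. No exclusion concerns a negative test that accompanies a COVID-19-coded admission.

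**The concern.** A code for COVID-19 without an identified virus is the less specific of the two codes. If part of these admissions are other illnesses, a booster should not prevent them, and counting them as events biases the severe-outcome rate ratio towards 1. The bias is not even over follow-up. It is greatest where true protection is greatest, shortly after the booster, so it flattens the waning curve that the trend test in 5.1.5 is meant to detect.

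Section 5.1.7 does not settle the matter. It proposes to consider a restriction to primary diagnosis, which moves the position of the code and leaves the code list as it is. A reader of the results could not tell how much rests on U07.2.

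The case-control part has a related gap. The SAP defines controls by a negative test but does not say that a severe case must have a positive one.

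**Working it through.** **Reading the definitions together.** Take a symptomatic patient with a negative RT-PCR, no positive test in the next 7 days, and an admission coded U07.2.

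- Cohort: 5.1.2 with Table S1 makes this a primary-outcome event.
- Sensitivity analysis in 5.1.7: if U07.2 is the primary diagnosis, the patient is still an event.
- Test-negative design: 5.1.5 makes the patient a control, and no exclusion in 3.5 applies. Whether the admission could also make the patient a severe case depends on a sentence that the SAP does not contain.

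**Size in the cohort.** The SAP states no figure to reproduce: no share of U07.2 admissions, no event count and no expected rate ratio. The following is an illustration.

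Inputs, all assumed:
- f = share of reference-period events that are not COVID-19: 2%, 5%, 10%, 20%.
- The booster has no effect on those events.
- True rate ratios of 0.10, 0.20 and 0.30.

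Formula: RR_obs = (1 − f) × RR_true + f × 1. The bias is f × (1 − RR_true), so it grows as RR_true falls.

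Example: with f = 5% and RR_true = 0.10, RR_obs = 0.95 × 0.10 + 0.05 = 0.145.

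| f | RR 0.10 seen as | RR 0.20 seen as | RR 0.30 seen as |
|---|---|---|---|
| 0% | 0.10 | 0.20 | 0.30 |
| 2% | 0.118 | 0.216 | 0.314 |
| 5% | 0.145 | 0.24 | 0.335 |
| 10% | 0.19 | 0.28 | 0.37 |
| 20% | 0.28 | 0.36 | 0.44 |

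**Effect on waning.** Suppose the true rate ratio is 0.10 early and 0.30 late, a late-to-early ratio of 0.30 / 0.10 = 3.0. From the table, the observed ratio is:
- f = 2%: 0.314 / 0.118 = 2.66
- f = 5%: 0.335 / 0.145 = 2.31
- f = 10%: 0.37 / 0.19 = 1.95
- f = 20%: 0.44 / 0.28 = 1.57

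**When some U07.2 admissions are real cases.** Only the non-COVID part counts towards f. If U07.2-only admissions were 10% of reference-period events and half were real COVID-19, then f = 10% × 0.5 = 5%, and a true 0.10 would be seen as 0.145 instead of 0.19.

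**With U07.2 out of the code route**, f from this source is 0 and RR_obs = RR_true in this model.

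**The case against.** The strongest objection concerns the test-negative design. A reader might infer that the case and control groups are shown to overlap. The documents do not support that. A test-negative design ordinarily has test-positive cases. Section 5.1.5 measures time since vaccination from the sample date for cases and controls alike, and the outcome wording in 5.1.2 speaks of time to an event, which is cohort language. The natural reading of the first objective is people who tested positive and were then admitted or died. What remains is an unstated requirement, which calls for clarification only.

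A reader might also equate U07.2 with a negative test, or with not having COVID-19. Table S1 says only that the virus was not identified. The label could cover patients with no test or no result, and some will be true cases. This stands: dilution follows only for the part that is not COVID-19.

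The shares are hypothetical. At the low end the effect is small (0.20 becomes 0.216), and nothing in the SAP shows that 20% is plausible. This stands too.

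A limit to Scotland is tempting, because footnote 2 confines ICD use to Scotland. That footnote covers deaths only. For hospitalisation, 5.1.2 names no country, so the limit is an inference.

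Section 5.1.2 does not cite Table S1, but it relies on COVID-19 codes and no other list is given. Sections 5.1.7 and 5.1.8 offer some protection (primary diagnosis only, a shorter interval from onset to test, non-COVID admissions as a negative control). All are things to be considered, and none isolates U07.2.

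**Conclusion.** The point holds for the primary outcome. As written, the plan admits admissions without virus confirmation as events, and no planned analysis separates them. The direction is towards a rate ratio of 1 and towards understated waning, on two assumptions: that some U07.2 admissions are not COVID-19, and that the booster does not affect those. The size is unknown. An assumed 2% to 20% of reference-period events moves a true 0.10 to between 0.12 and 0.28, and a true 0.20 to between 0.22 and 0.36. These figures are a range of what-ifs and not an estimate for either country.

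The missing positive-test requirement for severe test-negative-design cases is secondary. Overall this is a cheap improvement to make before analysis and does not show that the design fails.

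**What to change.** - **5.1.2 and Table S1:** limit the code route of the primary outcome to U07.1. Report a sensitivity analysis that adds U07.2. Apply the same rule to ICD-coded deaths. State which country's hospitalisation data use the code route.
- **5.1.5:** state that test-negative-design cases require a positive test.
- **3.5:** exclude from the controls any negative test followed within 14 days by a COVID-19-coded admission (U07.1 or U07.2). The window matches the one between test and admission in 5.1.2.

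The cost is a few lines in four places and one extra model run. The downside is that some true but unconfirmed COVID-19 admissions leave the primary outcome. If the missed share does not depend on booster status, that costs precision and leaves the rate ratio unbiased, whereas false events bias it. The SAP gives no event counts, so the loss of precision cannot be computed. With 10 million and 5 million boosted people expected in Brazil (section 3.6) it should be small there; no Scottish figures are given. The sensitivity analysis with U07.2 would show how much the choice matters.
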